### Sub-study 1: data collection and analysis

A combination of qualitative methods will be used to address RQ1–4 and to ensure the external validity of the experiment (Sub-study 2) by basing it on empirical data [20]. First, fidelity–adaptation dilemmas (RQ1) will be explored through about 10 individual interviews with parental program practitioners, aimed at understanding how practitioners describe typical fidelity–adaption dilemmas. Throughout the study, the numbers of interviews will depend on the richness and complexity of the data [48]. This means that the numbers of respondents cannot be determined beforehand.

Second, sequential focus group interviews [49] with 4–8 participants in each group will be conducted to explore the alternatives between which practitioners choose (i.e., options [RQ2]) and the outcomes that influence their choices (i.e., attributes [RQ3a]). Inspired by the procedure of Coast and Horroks for exploring attributes [50], we will use an iterative approach whereby data collection and analysis proceed concurrently. Once the analysis indicates that options have been thoroughly explored, we will gradually shift the emphasis from primarily investigating options in the initial focus groups to the outcomes that are valued with those options (i.e., the attributes). This shift also entails moving from a fully explorative approach in the first focus group, in which no option has yet been identified, to a sequential interview format, in which the exploration of options is followed by the presentation of the options identified in previous focus groups. This approach allows the exploration of the anticipated outcomes of all options and the way in which they are valued. With this iterative approach, there is no fixed set of focus groups planned in advance. Based on previous research, we anticipate three to four practitioner focus groups [51]. Another two to three focus groups of parents and decision-makers, respectively, will be formed to explore how these stakeholders appraise the value of parental groups (RQ3b).

Third, another round of *individual interviews* with practitioners (RQ4) will be conducted. Previously collected data will be used as input to elicit information about the value conflicts and the associated trade-offs that practitioners experience. The interviews will include two phases, inspired by Grundstein et al.’s study on ethical decision-making [52]. First, the participants will be asked to describe critical incidents in which they had to make a decision related to the fidelity–adaptation dilemma and the value trade-offs involved. Second, the dilemmas and associated options and valued outcomes identified in the previous steps will be presented, and value conflicts will be explored. In this, we will also collect data on how each outcome varies, which will subsequently inform the selection of response categories (i.e., levels) for the attributes when constructing the experiment (RQ5). Data collection, transcription, and analysis will be conducted iteratively. We estimate that 15–20 interviews will be required.

#### Data analysis

Data from all qualitative methods in Sub-study 1 will be analyzed using reflexive thematic analysis [53, 54]*.* The interviews will be recorded and transcribed verbatim. Two persons will conduct the analysis and reflectively compare each other’s interpretations of the data. To evaluate the study’s trustworthiness, Guba and Lincoln’s [55] criteria and recommendations for verification strategies will be used. The remaining researchers will act as informed outsiders.

### Sub-study 2: data collection and analysis

After exploring the parameters underlying decisions about fidelity and adaptation, to address RQ5, we will conduct a discrete choice experiment using an online survey to test how different combinations of attributes and levels affect choices [20].

The experiment will mimic real-world decisions. Practitioners will make decisions based on a holistic appraisal of two options—adhering or adapting. The options differ in terms of combinations of attribute levels—that is, they offer some outcomes with more value and others with less (i.e., different configurations of values). The value configuration will serve as the independent variable, and the choice between adhering or adapting will be the dependent variable. In the hypothetical example shown in Table 1, the attributes (outcomes) are efficacy, timeliness, and two types of adverse outcomes—one related to those receiving the EBI and one related to those not receiving it, and the dependent variable is adherence to or adaptation of the program.

**Table 1 Tab1:** A hypothetical example of a survey question in the discrete choice experiment

Scenario: The parental program includes 10 sessions, seven focusing on improving parental skills in general and parent–child relationships in particular, and three focusing directly on child behavioral problems. Each group includes six parents, and due to constraint resources, the practitioners can only accommodate 21 sessions per year. There is a long waiting list.		
**Outcomes**	**Option 1: Provide all 10 sessions**	**Option 2: Omit three sessions**
Efficacy	Parental skills are improved, and relational and behavioral issues are solved.	Parental skills are improved, and relational issues are solved, but behavioral problems remain.
Timeliness	Twelve parents a year are treated.	Eighteen parents a year are treated.
Adverse outcome, participants	One chance in 20 that behavioral problems will deteriorate to delinquency.	One chance in 10 that behavioral problems will deteriorate to delinquency.
Adverse outcome, waiting list	One chance in 10 that children on the waiting list develop anxiety disorder.	One chance in 20 that children on the waiting list will develop anxiety disorder.
**Which option would you choose?**	**Option 1**	**Option 2**

#### Experimental survey development

Scenarios (i.e., typical dilemmas; RQ1), options (RQ2), attributes (RQ3), and the response categories that are relevant to an attribute (i.e., levels; RQ4) will be identified through the preceding qualitative steps (Sub-study 1). A central part of the experiment consists of the determination of the number of scenarios and questions in the survey. The number of possible combinations of attributes and levels increases exponentially (e.g., five attributes with five levels each equals 3125 combinations). Therefore, we will use a fractional factorial experimental design. This involves reducing the number of combinations statistically [56].

If the pre-work indicates that some value judgments do not vary meaningfully, we may opt for a partial profile design, in which the level of specific attributes is held constant [57]. This will also be done if there are more than five to six outcomes associated with a specific scenario to reduce the cognitive load associated with judging a large number of attributes [57] and to minimize the risk of the survey being perceived as too time-consuming and/or difficult [58].

The experiment will include approximately four scenarios, each with a number of questions where the respondent will be asked to choose between two or more options (i.e., *option-choice questions*). We will aim for around 96 option-choice questions, 24 for each dilemma. Each respondent will be randomly assigned to one of six versions, meaning that each participant will respond to 16 questions, four per scenario. Up to 16 questions are commonly used as a trade-off between cognitive load and data acquisition [59]. The sequence of scenarios will be randomized. For each question, participants will be asked to indicate how certain they are about their choice, to assess choice certainty [60]. In addition, the stability and rationality of responses will be tested. Choice consistency (if the same choice is made twice) will be tested by repeating one question in each survey, and rationality by including a discrete choice comparison where one alternative is superior to the other (choice monotonicity) [60]. Data collected through the survey will also include demographic information, education, professional experience, and experience in evidence-based parental programs.

#### Data collection

After careful pilot testing, participants will be sent emails with a link to a secure web-based survey. The required sample size for an experiment depends on the numbers of choice tasks, alternatives, and analysis cells [59]. A rule of thumb is that a sample size of over 100, or 20 respondents per questionnaire version (six in this case), is required [59]. Based on this, we aim for at least 120 respondents, which we deem feasible given that, according to a conservative estimate, at least 1000 practitioners work on parental programs in Sweden.

#### Data analysis

The data will be analyzed using random parameters logit or multinomial logit models, depending on whether the scenario includes a choice between two or more than two options. Nested models may be an alternative if they better reflect how decisions are made (i.e., if decisions follow a decision-tree structure). We will use effect coding rather than dummy coding, as this allows the estimation of effect sizes for each attribute level. Individual utility profiles will be modeled, from which we will estimate parameters reflecting which option practitioners prefer, including the magnitude, sign, and statistical significance of coefficients; the relative importance of different outcomes; how the configurations of values influence choices; how changes in value configurations affect the probability of a certain decision; and willingness to trade—that is, what a person is willing to give up in one outcome to improve another (the marginal rate of substitution) [56].

Differences in decisions between stakeholders and practitioners with different levels of experience will be analyzed through split-sample analysis using Log likelihood Chow tests to examine whether preferences differ between subgroups.

To determine trade-off levels, we will calculate the maximum acceptable risk (from preference weights)—that is, the greatest risk that participants are willing to accept for a given outcome or the marginal rate of substitution. The experiment will thus provide information on which decision, given the known value configurations, represents the optimal balance between the different outcomes.

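### Random parameters or multinomial logit is chosen by the number of options, but the choice should rest on repeated choices and differences between respondents

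*Protocol article*

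**What the plan says.** Under Sub-study 2, the Data analysis section of the protocol article says the choices will be analysed with "random parameters logit or multinomial logit models, depending on whether the scenario includes a choice between two or more than two options". It adds one alternative: "Nested models may be an alternative if they better reflect how decisions are made", meaning where decisions follow a tree. The same paragraph promises individual utility profiles, without limiting them to some scenarios, and says the statistical significance of coefficients will be reported.

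The opening of Sub-study 2 describes a two-option task: "Practitioners will make decisions based on a holistic appraisal of two options—adhering or adapting". Experimental survey development is wider and has respondents "choose between two or more options". On volume, that section says "We will aim for around 96 option-choice questions, 24 for each dilemma", then "Each respondent will be randomly assigned to one of six versions", so that "each participant will respond to 16 questions, four per scenario". The Data collection section gives the target: "we aim for at least 120 respondents".

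**The concern.** The rule ties the model to a feature that does not separate the two models. Both can be fitted to two options or to more. They differ in whether coefficients vary between respondents, and so in whether one person's answers may be correlated. The design creates that correlation in every scenario, because every respondent answers several questions about it.

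Three things are at stake for the scenarios that the rule sends to multinomial logit:

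- the individual profiles cannot be produced;
- coefficients cannot be compared directly with those of scenarios analysed by random parameters logit;
- standard errors, and the significance statements built on them, are too optimistic unless clustering by respondent is added.

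Sub-study 2 answers the project's only experimental question (RQ5), and its results are the input to the Sub-study 3 focus groups.

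**Working it through.** **Step 1: the plan's own counts.** 96 questions / 6 versions = 16 per respondent. 24 per dilemma / 6 = 4 per scenario. 6 versions × 20 respondents = 120. All agree with the article. One scenario therefore yields 120 × 4 = 480 choices.

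**Step 2: what the number of options decides.** For respondent n, question t and option j among J options, with attribute levels x:

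P(n chooses j at t) = exp(β_n·x_ntj) / Σ_k exp(β_n·x_ntk), with k running over the J options.

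- Multinomial logit sets β_n = β for everyone. With J = 2 it is the ordinary binary logit.
- Random parameters logit gives β_n a distribution across respondents. Its panel form integrates the product of one person's four choice probabilities over that distribution.

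J enters only through the sum in the denominator. Whether β_n varies is a separate matter, so either model goes with either J.

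**Step 3: the two ways to read the sentence.**

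| Reading | Two options | More than two options |
|---|---|---|
| In order | random parameters | multinomial |
| Reversed | multinomial | random parameters |

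In both rows one class of scenario gets a model with a single β. A single β contains no person-level quantity, so individual profiles cannot be derived for that class. This follows from the text alone and needs no simulation.

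**Step 4: size of the effect on tests.** The article gives no alpha, effect sizes or heterogeneity, so these are assumptions:

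- 120 respondents, 4 choices each, 1,000 runs per setting;
- one adherence constant (mean 0.3) and four two-level effect-coded attributes, one with mean effect 0 and three with mean 0.5;
- normal person-level coefficients, all with the same between-person SD of 0, 0.5 or 1.0 logits;
- attribute levels drawn at random rather than from a fixed six-version design.

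With a mean effect of 0.5, an SD of 0.5 puts Φ(−0.5/0.5) = 16% of people on the opposite side of zero. An SD of 1.0 puts Φ(−0.5/1.0) = 31% there.

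Rejection rate of a two-sided nominal 5% test of the attribute with mean effect 0, multinomial (or binary) logit:

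| Options | SD | Model-based errors | Clustered errors |
|---|---|---|---|
| 3 | 0 | 5.5% | 5.2% |
| 3 | 0.5 | 8.8% | 5.6% |
| 3 | 1.0 | 14.0% | 6.6% |
| 2 | 0 | 5.6% | 5.1% |
| 2 | 0.5 | 7.3% | 5.3% |
| 2 | 1.0 | 8.6% | 5.9% |

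The Monte Carlo standard error is √(0.05 × 0.95 / 1000) = 0.7 percentage points near 5%, and √(0.14 × 0.86 / 1000) = 1.1 points near 14%. With three options, the empirical SD of the estimate over the mean model-based standard error was 0.063/0.063 = 1.0, 0.067/0.060 = 1.1 and 0.075/0.058 = 1.3 at SDs of 0, 0.5 and 1.0.

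**Step 5: size of the effect on the coefficients.** With three options, a true mean of 0.50 was estimated on average as 0.504, 0.376 and 0.252 at SDs of 0, 0.5 and 1.0. The last two are 0.376/0.50 = 75% and 0.252/0.50 = 50% of the true mean. With two options the averages were 0.506, 0.360 and 0.225. Clustering changes the standard error and leaves the estimate where it is.

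**The case against.** Several points can fairly be made for the plan.

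- **The sentence has no *respectively*.** A reader might infer that multi-option scenarios will certainly get the multinomial logit. The text does not settle this. The criterion is wrong on either reading, but which scenarios suffer is open.
- **There may be no multi-option scenarios.** The opening description and Table 1 show two options, and the options come out of Sub-study 1. On the ordered reading every two-option scenario already gets random parameters, so the harm is conditional. The point stands because the survey section allows more than two options and the rule exists to cover that case.
- **The article does not say how standard errors are computed.** A reader might infer that repeated choices will be treated as independent. That is not stated, and clustering is a detail an article may leave to a fuller plan. The error rates above therefore describe what happens if clustering is absent. The missing individual profiles and the difference in scale do not depend on it.
- **All 16 choices might be thought to enter one model,** where the inflation would be larger. The article picks the model by scenario and describes no pooled model, so four choices per person is the relevant case.
- **Nested models are offered.** They are reserved for tree-structured decisions, and nothing says they would be applied to two-option questions, so there is no error in that sentence. They can relax the assumption about similar options, but by themselves they do not let preferences vary between people.
- **Ratios are more robust.** Part of the shrinkage in Step 5 may cancel in a marginal rate of substitution. This softens the consequence for trade-offs, but not for the coefficients themselves.

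**Conclusion.** The criterion is wrong and should be corrected before analysis. Two consequences follow from the text whichever way the sentence is read, provided some scenario is sent to multinomial logit: that scenario cannot yield the promised individual profiles, and where preferences differ between people its coefficients are on a different scale from those of scenarios analysed with random parameters.

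The third consequence, liberal tests, is conditional on unclustered errors and on heterogeneity. It amounts to about 9% to 14% instead of 5% per scenario with three options, and about 7% to 9% with two, at assumed SDs of 0.5 to 1.0 logits. With no heterogeneity there is no inflation.

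This is a should-fix point. It concerns one analysis sentence, leaves the design and the target of 120 untouched, and can be repaired without new data.

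**What to change.** Replace the selection rule with: *All scenarios, whatever the number of options, will be analysed with a panel random parameters (mixed) logit with respondent-level random coefficients; a multinomial (or binary) logit with respondent-clustered standard errors will be the base model, and the fallback where the random parameters model does not converge.* The sentence on nested models can stay.

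If the fallback is used for a scenario, the report should say that individual profiles are not available there.

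The cost is somewhat wider intervals, longer computing and possible estimation difficulty. The panel random parameters model was not fitted in the simulation, so its stability here is untested. As an illustration, five attributes with five levels (the article's own example of how combinations multiply) give 5 × (5 − 1) = 20 effect-coded coefficients. If all were random and independent, that would mean 20 means and 20 SDs, or 480 / 40 = 12 choices per parameter in a scenario. The number of random coefficients may therefore have to be limited, and the plan should say beforehand which ones have priority.

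### Without a scale adjustment, the split-sample Chow test can report a preference difference between experience groups that differ only in how consistently they choose

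*Protocol article*

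**What the plan says.** In the protocol article, Data analysis under Sub-study 2, choices are modelled with random parameters logit or multinomial logit, according to whether a scenario offers two options or more. "Differences in decisions between stakeholders and practitioners with different levels of experience" are then to be examined in split samples, "using Log likelihood Chow tests to examine whether preferences differ between subgroups". So the article names both the test and the conclusion to be drawn from it. It gives no number of groups and no cut-points for experience, and it mentions no relative scale parameter. The same section plans marginal rates of substitution and maximum acceptable risk, but does not tie them to the subgroup comparison.

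The survey development section plans six versions and 16 questions per respondent, four for each of about four scenarios. It also plans a certainty rating per question, one repeated question and one dominance check.

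The data collection section says that sample size "depends on the numbers of choice tasks, alternatives, and analysis cells". It cites a rule of thumb that "a sample size of over 100, or 20 respondents per questionnaire version (six in this case), is required", and concludes that "we aim for at least 120 respondents".

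**The concern.** Logit models identify preference only up to scale. If less experienced practitioners choose more erratically, all their coefficients shrink towards zero even when their relative weighting of outcomes is the same as that of experienced colleagues. An unadjusted Chow test sees two different coefficient vectors and rejects.

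Experience is a plausible source of unequal choice noise, and it is the factor being split on. The survey collects certainty and consistency data that bear on noise, but the subgroup test makes no use of them.

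At stake is a statement that experienced and inexperienced practitioners value outcomes differently. Results of the experiment are also shown to the Sub-study 3 focus groups, so a misread noise difference could carry into that stage.

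**Working it through.** **The plan's own figures.** 20 respondents × 6 versions = 120, which reproduces the target. 96 questions / 6 versions = 16 per respondent, and 24 / 6 = 4 per scenario. No alpha, power or effect size is stated for the experiment, so there is no power figure to reproduce.

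**What the test compares.** For a choice between two options with attribute difference x, group g has P = 1 / (1 + exp(−μ_g x′β_g)), with preference β_g and scale μ_g. The data identify only the product b_g = μ_g β_g.

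- Unadjusted Chow test: LR = 2(LL1 + LL2 − LL_pooled) on K degrees of freedom. Its null hypothesis is μ1β1 = μ2β2. If β1 = β2 but μ1 ≠ μ2, that null is false and the test should reject.
- Scale-adjusted test: in the pooled model, multiply group 2's design by a free factor λ. Then LR = 2(LL1 + LL2 − LL_λ) on K − 1 degrees of freedom. Its null is that the coefficient vectors are proportional, which is what equal preferences means in a logit model.
- In the ratio (μβ_a)/(μβ_b) = β_a/β_b the scale cancels. Marginal rates of substitution are therefore unaffected.

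**How large the effect can be.** Assumptions that are not in the documents: alpha 0.05; two equal groups of 60; binary logit with independent choices within respondent; K = 5 or 9 parameters of moderate size; scale ratios from 1 to 3. Preferences are identical in every cell, so every rejection is false. There were 400 runs per cell, which gives a simulation standard error at 5% of √(0.05 × 0.95 / 400) = 1.1 percentage points. Entries are unadjusted test / test with scale freed.

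| Scale ratio | One scenario, 4 choices, K = 5 | 16 choices pooled, K = 5 | 16 choices pooled, K = 9 |
|---|---|---|---|
| 1.0 | 9% / 7% | 4% / 4% | 6% / 6% |
| 1.25 | 11% / 8% | 24% / 4% | 26% / 5% |
| 1.5 | 25% / 7% | 76% / 4% | 84% / 5% |
| 2 | 58% / 6% | 99% / 7% | 100% / 5% |
| 3 | 97% / 7% | 100% / 5% | 100% / 6% |

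A second simulation used a different design: five two-level attributes plus an adherence constant, 6 degrees of freedom, 500 runs. At ratios 1.5 and 2 it gave 20% and 40% per scenario, and 63% and 98% pooled. The exact rates move with the design and coefficients; the direction does not. Freeing the scale brings rejection to 4% to 8% throughout, which identifies scale as the cause.

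**Subgroup size at the target.** At exactly 120, two equal groups have 120 / 2 / 6 = 10 respondents per version, and three have 120 / 3 / 6 ≈ 6.7. Keeping 20 per version within each group would take 20 × 6 × 2 = 240 or 20 × 6 × 3 = 360.

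**The case against.** The strongest reply is that everything depends on a scale difference for which the documents give no figure. A reader might infer that groups with identical preferences will be declared different. That is not supported: at equal scale the test roughly holds its level, and at a ratio of 1.25 it rejects in 11% of cases per scenario. The survey's certainty and consistency checks show that noise will be measured, not that it varies with experience. This stands, and the point is about what can happen.

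Other strong readings also fail:

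- The near-certain rejection rates need one coefficient set across all scenarios. The article chooses the model by scenario and derives options and attributes from each dilemma, so the per-scenario column is the safer guide.
- Repeated choices could inflate the test further. With equal scale, a between-person SD of 0.5 and multinomial logit, simulated rejection is 9% per scenario and 28% pooled. But that model is fitted there to two-option choices, and the article, read in order, assigns random parameters logit to those and also plans individual utility profiles.
- A reader might say that each half breaches the plan's own minimum per version. That needs two equal groups, recruitment stopping below 240, and a rule given for the whole sample applied per subgroup. None of these is stated, 120 is a floor, and the article estimates a pool of at least 1000 practitioners. Naming analysis cells as a driver of sample size permits the per-subgroup reading but does not impose it.

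Finally, a scale-adjusted version might sit in an analysis plan that is not shown, and RQ5 does not ask about experience subgroups. Both limit the weight of the point. They do not remove it, because the article pairs a named test with a conclusion that the test, as described, cannot support.

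**Conclusion.** The point holds in conditional form. As described, the subgroup test confounds preference with choice consistency, so a rejection does not by itself show that preferences differ. The size rests on the assumed scale ratio: about 11% to 58% false rejection per scenario for ratios of 1.25 to 2, and about 24% to 99% if all 16 choices share coefficients. These rates come from plain binary logit with 60 per group. They were not computed for random parameters logit, although the confounding is the same there. The subgroup sample size is a supporting reason for caution and does not cause the false positives.

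**What to change.** Keep the split-sample comparison and add a scale step, following the Swait–Louviere sequence:

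1. Estimate a relative scale parameter in the pooled model and test equality of preferences with scale free, on K − 1 degrees of freedom for two groups.
2. Test equal scale only if preference equality is not rejected.

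Alternatively, compare subgroups on the marginal rate of substitution and maximum acceptable risk, which are already planned and free of scale. Under either route, fit the models with the panel structure of repeated choices per respondent, and label the comparison exploratory, since the target of at least 120 is not sized for subgroups.

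A single model with full attribute-by-experience interactions plus a scale term for experience group would not serve: the interactions already leave each group's coefficients unrestricted, so the scale term is not identified.

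The cost is a change of analysis wording and one extra parameter for a two-group comparison; experience is already collected. The price is somewhat lower power and a weaker subgroup claim. A group that weights every outcome proportionally more also cannot be told apart from one that chooses with less noise, and the report should say so.
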